## Abstract

**Background:**

Clinicians face challenges in promoting colorectal cancer screening due to multiple competing demands. A decision aid that clarifies patient preferences and improves decision quality can aid shared decision making and be effective at increasing colorectal cancer screening rates. However, exactly how such an intervention improves shared decision making is unclear. This study, funded by the National Cancer Institute, seeks to provide detailed understanding of how an interactive decision aid that elicits patient’s risks and preferences impacts patient-clinician communication and shared decision making, and ultimately colorectal cancer screening adherence.

**Methods/Design:**

This is a two-armed single-blinded randomized controlled trial with the target of 300 patients per arm. The setting is eleven community and three academic primary care practices in Metro Detroit. Patients are men and women aged between 50 and 75 years who are not up to date on colorectal cancer screening. ColoDATES Web (intervention arm), a decision aid that incorporates interactive personal risk assessment and preference clarification tools, is compared to a non-interactive website that matches ColoDATES Web in content but does not contain interactive tools (control arm). Primary outcomes are patient uptake of colorectal cancer screening; patient decision quality (knowledge, preference clarification, intent); clinician’s degree of shared decision making; and patient-clinician concordance in the screening test chosen. Secondary outcome incorporates a Structural Equation Modeling approach to understand the mechanism of the causal pathway and test the validity of the proposed conceptual model based on Theory of Planned Behavior. Clinicians and those performing the analysis are blinded to arms.

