### Aim 1: to measure the impact of CW on patient uptake of CRCS

H-1: patients in the intervention arm will have higher rates of CRCS adherence at the six month follow-up than those in the control arm.

The study arms will be compared to assure that randomization achieved similar study population with respect to age, gender, race, previous CRCS, practice site, and data completion. Medically documented completion of CRCS will be compared between the intervention arm and the control arm by means of a chi-square test (unadjusted analysis) and a logistic regression adjusting for potential predictors at baseline. The regression analysis will be performed with data at the patient level with completing CRCS (yes/no) as the outcome measure and the arm assignment (intervention arm versus control arm) as the main covariate of interest. The practice indicator will further be included as a covariate in order to account for the variation between practices. The clustering effect due to clinician will be accounted for by using a generalized estimating equations approach. Personal patient-level background information (for example, age, race, education, marital status, smoking, health status, health insurance) from the patient baseline survey will be considered for inclusion in the regression model. The model will further be adjusted for information about the patient’s past experience with the CRCS procedures and the baseline level of patient determinants (for example, knowledge, attitude, subjective norm, self-efficacy) and intent. We will also adjust for OPTION score and pertinent clinician-level covariates such as the clinician’s communication style from the clinician survey. In order to understand whether there is any difference in the completion of CRCS rates between groups of patients who (a) complete the risk assessment tool only, (b) complete the preference clarification tool only, (c) complete both, and (d) complete neither, we will use a four level factor indicating this group membership as an independent variable in the regression model.

The contribution of a specific group of covariates will be measured by means of increase in generalized R-square defined as:$$R^{2}\left(\mathrm{increase}\right)=\exp\left(-L_{1}^{2}/n\right)-\exp\left(-L_{2}^{2}/n\right)$$where $L_{1}^{2},L_{2}^{2}$ are the likelihood ratio statistics of the smaller and larger models, respectively.

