### Sample size and power

In aims 1, 2 and 3, we make comparisons between the intervention arm and the control arm. The effect size we wish to detect between the study arms is 15%. Based on published data [48], the estimated proportion of study participants in the control arm that will complete CRCS by six months post intervention is 10 to 15%. Based on the pilot randomized controlled trial, the proportion is slightly higher (approximately 24%). We take this higher value as the anticipated rate in the control arm after six months, since this gives more conservative (larger) sample size estimates. To detect with 90% power a 15% increase in the completion rate in the intervention arm to be significant, one needs to have 213 patients per study arm. The calculation is based on a two-sided continuity-corrected chi-square test of independent proportions with 5% type-I error rate. Since we target to recruit 300 patients in each study arm, with a rough balance across practice, race, and gender, we have good power to detect such differences in the gender subgroups as well. For example, assuming that we have 150 men in each study arm, we have 76% power to detect the effect size described herein. With 300 patients per arm, a standardized mean difference of 0.23 can be detected between the two arms for continuous outcomes with 80% power. For dichotomous outcomes such as concordance, a 15% difference between the two arms can be detected with a power of ≥ 80%, when the percentage of occurrence in the control arm ranges between 25% and 50%. Thus, we are adequately powered to detect small differences for all aims. For the Structural Equation Modeling analysis, we estimate that the conceptual model will have > 100 degrees of freedom. Assuming a sample of 600 patients, power will be > 99% for a test of the overall model. Power to reject the model will be assessed by root mean square error of approximation [83].

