### Dissemination

The participating clinicians receive regular newsletters and Email updates about the study. Upon completion of the study and analysis of data for the primary hypothesis, the participating clinicians will receive a summary report and be invited to meet with the PI for discussion. The participating patients will receive a summary letter about the results. Updates about the findings will be posted in each participating clinical site.

The data including audiotapes will be open to other investigative teams for additional analysis by contacting the PI with a formal request. Contact information will be provided with all presentations and publications. The request form is available as Additional file 8. Each request will be reviewed by the research team and the Data and Safety Monitoring Committee for approval.

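### Six outcomes are labelled primary while other sections speak of one primary hypothesis, that hypothesis has two tests and no decider, and power is stated without allowance for multiplicity

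*Protocol article*

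**What the plan says.** - **Abstract, Methods/Design.** The list opens "Primary outcomes are patient uptake of colorectal cancer screening; patient decision quality (knowledge, preference clarification, intent" and ends with the clinician's "degree of shared decision making; and patient-clinician concordance in the screening test chosen". That is six items: uptake, knowledge, preference clarification, intent, SDM and concordance. Only the structural equation modelling is called secondary.
- **Abstract, Discussion.** One central hypothesis is given: the decision aid raises screening adherence, acting through patient factors, SDM and concordance.
- **Dissemination.** Results go to clinicians "Upon completion of the study and analysis of data for the primary hypothesis". The singular is used and the hypothesis is not identified.
- **Analysis, Aim 1.** Documented completion is compared "by means of a chi-square test (unadjusted analysis) and a logistic regression adjusting for potential predictors at baseline". The regression uses generalized estimating equations (GEE) for clustering by clinician, and it also adjusts for the OPTION score.
- **Variable selection.** A covariate stays in the model if it is significant for the outcome or if it moves the arm coefficient by more than 5%.
- **Sample size and power.** 213 per arm is derived for screening completion: "The calculation is based on a two-sided continuity-corrected chi-square test of independent proportions with 5% type-I error rate". The section then gives a detectable standardized mean difference (SMD) of 0.23 for continuous outcomes and at least 80% power for a 15-point difference in outcomes such as concordance. It concludes that power is adequate for all aims.

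**The concern.** The choice of primary outcome belongs in the protocol, and this article gives two answers. Under one, the trial stands or falls on screening uptake, and the other five outcomes are steps on the way to it. Under the other, six outcomes have equal standing, and nothing says whether one success is enough or all six are needed. A null result on screening could then be presented as a positive result on an outcome that the abstract calls primary.

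H-1 has a similar gap. Its two tests need not agree. The covariates of the adjusted model are chosen partly by how far they move the treatment effect. That model also conditions on the OPTION score, which is measured after randomization on a variable that the conceptual model places between intervention and screening. Its arm coefficient therefore leaves out whatever effect passes through SDM, so it does not answer the same question as the chi-square test.

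**Working it through.** **1. The plan's own sample size.** Inputs from Sample size and power: control rate 24%, difference 15 points (so 39%), 90% power, two-sided 5%, continuity correction. Mean rate 0.315.

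n0 = [z(0.975) × √(2 × 0.315 × 0.685) + z(0.90) × √(0.24 × 0.76 + 0.39 × 0.61)]² / 0.15²
= [1.960 × 0.6569 + 1.282 × 0.6483]² / 0.0225 = 199.5

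With continuity correction: (199.5/4) × [1 + √(1 + 4/(199.5 × 0.15))]² = 212.6, so **213 per arm**. This matches. The same test at 300 per arm has 97.3% power, and at 150 per arm 76.5% (the article says 76%).

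**2. Which alpha lies behind the other power statements.** Detectable SMD with 80% power and 300 per arm:
- two-sided 5%: (1.960 + 0.842) × √(2/300) = 0.229, the article's 0.23
- 5% split over six outcomes (0.00833): (2.638 + 0.842) × √(2/300) = 0.284

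The continuous outcomes were therefore powered at an unadjusted 5% each. For a 15-point difference in a dichotomous outcome, power is 97% (control rate 25%) and 95% (control rate 50%) at 5%, and 89% and 84% at 0.00833. Both sets meet the stated 80%, so that statement does not reveal its alpha.

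**3. Any one of six outcomes counts as success.** With independent tests at 5%: 1 − 0.95^6 = 0.265. The article gives no correlations, so a range is assumed and simulated with equally correlated two-sided z-tests:

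| Assumed pairwise correlation | At least one false positive |
|---|---|
| 0 | 26.5% |
| 0.3 | 24.0% |
| 0.5 | 20.8% |
| 0.8 | 13.9% |

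**4. The better of the two H-1 tests counts.** Simulated for assumed correlations between the two test statistics:

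| Assumed correlation | Type-I error |
|---|---|
| 0.98 | 5.9% |
| 0.95 | 6.5% |
| 0.90 | 7.0% |
| 0.80 | 7.8% |

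These figures leave out the data-driven covariate selection, whose effect cannot be computed from the article.

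**5. Price of Holm's method for the remaining comparisons.** After H-1 there are eight arm comparisons: four determinants under H2-1, then H2-2, H2-3, H3-1 and H3-2. The strictest step uses 0.05/8 = 0.00625. Detectable SMD: (2.734 + 0.842) × √(2/300) = 0.292.

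**The case against.** The strongest reply is that this is a condensed article, and a multiplicity rule commonly sits in the statistical analysis plan, which is not shown. That stands: the missing rule is not the finding. What remains is a conflict within the article about how many primary claims there are, and an analysis of H-1 that is described but not fixed.

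It can also be said that a lead hypothesis is visible: Aim 1 is uptake, the central hypothesis is adherence, and the 213 rests on a chi-square test of completion. This is fair and supports the fix below, but the abstract's list still says otherwise.

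Some stronger readings are tempting, and the article does not support them:
- **That every primary outcome is tested at 5%.** This is not written. The 5% is stated for screening completion only. It follows from the 0.23 for continuous outcomes and cannot be confirmed for the other dichotomous ones.
- **That the trial is sized on completion alone.** The 213 is, but the same section gives power for the other outcomes too.
- **That the error rate is 37%** (1 − 0.95^9). This counts attitude, subjective norm and self-efficacy, which the abstract does not list as primary, and it assumes independence among outcomes that the article places on one causal pathway.

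**Conclusion.** The point holds as a contradiction about the primary outcome and a poorly fixed test of H-1. A reader might infer that the stated 5% is false. It is not: it is right for the single chi-square test, and tests on other outcomes do not change it.

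Inflation arises only under two uses that the text leaves open. If any one of the six outcomes may carry the claim, the error is 13.9% to 26.5%. If the better H-1 test may be chosen, it is 5.9% to 7.8% before covariate selection. Both ranges rest on assumed correlations. If all six outcomes had to succeed, type-I error would not rise, though power would fall. The two-test part is the smaller in numbers. It still matters, because adjusting for the OPTION score changes what the arm coefficient measures.

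**What to change.** Before analysis begins (the article schedules it for April 2015 to March 2016):

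1. Name documented screening completion at six months (H-1) as the single primary outcome, and bring the abstract's list, the central hypothesis and the Dissemination wording into line.
2. Name one deciding test at two-sided 5%: the logistic GEE model with clustering by clinician, adjusted for the stratification factors practice, gender and race, without the OPTION score and without data-driven covariates. Keep the chi-square test as supportive.
3. Make the eight Aim 2 and Aim 3 arm comparisons secondary, tested with Holm's method.

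**Cost.** No extra patients are needed: alpha for H-1 and the 213 per arm are unchanged. The 97% power at 300 per arm belongs to the continuity-corrected chi-square test and should not be quoted for the GEE model. For the secondary outcomes, the SMD detectable with 80% power at Holm's strictest step rises from 0.23 to about 0.29. Because 339 of 600 patients had been recruited by 28 October 2013, relabelling five named primary outcomes is a mid-trial change and should be recorded with its date.

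**If six primary outcomes are really meant,** say so and split the 5%. A Bonferroni split needs 306 per arm for 90% power on completion. The planned 300 gives 89.3%, and power for 150 men per arm falls from 76% to 51%.

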## Methods/Design

The study is a two-armed randomized controlled trial with a target of 300 patients per arm. The intervention arm is CW, the web-based interactive DA that contains personal risk assessment and preference clarification tools. The control arm is SW, a non-interactive website that matches CW in design and content except for the omission of interactive risk assessment and preference clarification tools. It should be noted that most US primary care practices do not routinely use web-based DAs. SW in the control arm was created to rigorously assess the effect of the interactive features in CW on the outcomes detailed in the Aims section. The study protocol received ethical approval from the University of Michigan Institutional Review Board (HUM00044733).

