### Data collection instruments

Table 2 summarizes the data collection instruments with respect to source and time point of collection. Post-web survey will include manipulation-check questions. Also, data regarding patient’s CW/SW usage will be retrieved. They will allow us to check whether the patients in the intervention arm actually used the interactive tools in CW and found them to be useful. A more detailed table that correlates each question of the surveys with the domains of the conceptual model is included in Additional file 7.

**Table 2 T2:** Mediators and outcomes and data collection points

	**Patient survey**			**Clinician survey**	**Digital audio recording of patient visit**	**Endpoint chart audit**
	**Baseline**	**Post**-**web**	**Post**-**encounter**			
Demographic data (BRFSS)	×			×		
Past experience	×					
Knowledge	×	×				
Attitude	×	×				
Subjective norm	×	×	×			
Perceived self efficacy	×	×				
Patient preference	×	×	×			
Manipulation-check questions		×				
Clinician decision making Style				×		
Shared decision making			×		×	
Concordance			×		×	
Patient intention	×	×	×			
Action (CRCS)						×
Method of collection	web	web	paper	paper	recording	medical chart

x: Signifies that the mediators and outcomes in question were addressed in the survey, recording or audit.

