### Variable selection

In view of a potentially large number of candidates for inclusion as covariates, we will use a simple screening method as follows. Each potential covariate will be investigated for *confounding* effect by running a preliminary screening analysis with and without the covariate in the model along with the study arm and retaining the ones for the final logistic regression model, which either: (a) have a significant effect on the outcome; or (b) change the co-efficient of the study arm variable by more than 5%. *Moderating* effect of a potential covariate × will be investigated by including a study arm × interaction term in the model.

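### The unqualified statement that analysts are blinded to arm cannot hold through the Aim 1 analysis as written, because the planned tool-completion factor can take three of its four levels only in the ColoDATES Web arm

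*Protocol article*

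**What the plan says.** Five places in the protocol article bear on this.

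- **Abstract, Methods/Design:** "Clinicians and those performing the analysis are blinded to arms". No data set, stage or end-point is attached to the statement.
- **Methods/Design, opening paragraph:** the control site SW "matches CW in design and content except for the omission of interactive risk assessment and preference clarification tools".
- **Analysis, Aim 1:** patients are grouped as those who "a) complete the risk assessment tool only, (b) complete the preference clarification tool only, (c) complete both, and (d) complete neither", and "we will use a four level factor indicating this group membership as an independent variable in the regression model".
- **Variable selection:** candidate covariates are examined by "running a preliminary screening analysis with and without the covariate in the model along with the study arm". A covariate is kept if it is significant for the outcome or if it would "change the co-efficient of the study arm variable by more than 5" per cent.
- **CW and SW data retrieval protocol; Data collection instruments:** page-level usage is logged on both sites and is put to a stated use within one arm: "They will allow us to check whether the patients in the intervention arm actually used the interactive tools in CW".

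**The concern.** A blind on the analysts survives only if nothing in their data identifies the arm. Here a planned explanatory variable does identify it. A patient recorded as having completed the risk tool, the preference tool or both must have been given CW. A neutral A/B coding of arm gives no protection once that variable sits beside it.

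What is at stake is the discretion that remains in the modelling. The candidate covariates for H-1 are listed by example rather than exhaustively, and the clinician-level ones are described only as pertinent. Retention depends partly on how far the arm coefficient moves. H-1 also has both an unadjusted and an adjusted result. The plan for H3-1 is said to be identical to Aim 1, and those for H3-2 and H3-3 similar. An analyst who knows which code is CW can see which inclusion decisions favour it, and the abstract tells readers that analysts do not know.

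**Working it through.** The plan gives no figure on this point, so the check is a logical one followed by a count.

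**Step 1: who can occupy each level.** SW has no risk tool and no preference tool (Methods/Design). Of the four levels in Aim 1, risk tool only, preference tool only and both are therefore possible only in CW. Every SW patient falls in the level for neither. CW patients who skipped both tools join them there.

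**Step 2: how many patients the factor identifies directly.** Inputs: 300 patients per arm (Methods/Design), and u, the share of CW patients who complete at least one tool. The document does not give u, so a range is assumed.

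- CW patients identified with certainty = 300 × u
- Probability that a patient in the neither level is SW = 300 / (600 − 300 × u)

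| Assumed u | Identified as CW | Chance that a patient in the neither level is SW |
|---|---|---|
| 5% | 15 | 300/585 = 51% |
| 50% | 150 | 300/450 = 67% |
| 90% | 270 | 300/330 = 91% |
| 100% | 300 | 300/300 = 100% |

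This is what the factor discloses with no arm code in the file.

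**Step 3: what it does to a masked arm code.** If the file also holds arm as A or B, a single completer shows which letter is CW, and that decodes all 600 patients. The code stays masked only if no CW patient completes a tool. Treating u as each patient's independent chance of completing one, that probability is (1 − u)^300. At u = 5% it is 0.95^300 ≈ 2 × 10⁻⁷, and it is smaller for any larger u. The result hardly depends on the unknown u.

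**Step 4: other fields.** Page-level access logs that include the tool pages disclose the arm in the same way. The check described under Data collection instruments is framed within the intervention arm, so whoever runs it must know the arm.

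**Step 5: is the factor present when covariates are screened?** The Aim 1 text names as candidates the baseline characteristics, past screening experience, baseline determinants and intent, the OPTION score and clinician covariates. The tool factor comes afterwards, in its own sentence, to answer its own question. Neither Aim 1 nor Variable selection says that it is screened, or that it is in the file used for "retaining the ones for the final logistic regression model". No section describes the analysis file, masked codes or the order of runs.

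**Step 6: sample size.** The stated 213 per arm reproduces from 24% versus 39%, two-sided 5%, 90% power, with continuity correction (200 without it). Nothing in this point alters it.

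**The case against.** The strongest reply is that the passages are compatible. A masked covariate screen and arm comparison could come first, with the tool-use analysis after unmasking. The order of data release is the kind of detail an article may leave to a fuller document. This stands against a stronger reading that a reader might infer, namely that the covariate screen itself is run on data that disclose the arm. The article does not establish that. It does not rescue the abstract's sentence, which covers those performing the analysis without limit, while the tool factor is assigned to the regression for Aim 1.

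A second reply is that the sentence may only summarise the blinding of the OPTION observers, since the body of the article describes blinding for them and for clinicians but not for statisticians. That is possible and cannot be ruled out. If it is so, the sentence is too broad and should say what it means.

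A third reply is that little bias could follow. The retention rule is fixed in advance and largely mechanical, the unadjusted chi-square test involves no covariate selection, and the endpoint is a medically documented procedure with fixed coding. All of this stands and keeps the point small. Some discretion remains because the pool of candidate covariates is open.

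**Conclusion.** The point holds as a contradiction between a stated property of the trial and its planned analysis: analysts cannot remain blinded to arm while working with the tool-completion factor or the tool-page usage data. Where a masked arm code sits in the same file, disclosure is effectively complete. This rests on two things: SW contains neither tool, as the article says, and at least one CW patient completes a tool, which is near certain at any plausible rate of use.

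It would go too far to conclude that the H-1 model is selected unblinded or that any estimate is biased; neither is shown. Severity is low: the credibility of a blinding claim is affected, not an effect estimate, an error rate or the power.

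**What to change.** Preferred: stage the analysis and say so. Run and lock the covariate screen and the H-1, H2 and H3 arm comparisons on masked arm codes, in a file without the tool-completion factor, the usage logs and any other field that only CW patients can have. Then unmask and release those fields for a separate tool-use analysis.

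Alternative: reword the abstract's sentence so that it names the stage, or the people, to whom the blind applies, or withdraw the claim for analysts.

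The first option costs a two-step data release and the second a corrected sentence. Neither needs new data or changes the sample size.
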